# A double-blind randomised controlled trial of a natural oil-based emulsion (Moogoo Udder Cream®) containing allantoin versus aqueous cream for managing radiation-induced skin reactions in patients with cancer

**DOI:** 10.1186/1748-717X-7-121

**Published:** 2012-07-31

## Abstract

**Background:**

Radiation-induced skin reaction (RISR) is one of the most common and distressing side effects of radiotherapy in patients with cancer. It is featured with swelling, redness, itching, pain, breaks in skin, discomfort, and a burning sensation. There is a lack of convincing evidence supporting any single practice in the prevention or management of RISR.

**Methods/Designs:**

This double-blinded randomised controlled trial aims to investigate the effects of a natural oil-based emulsion containing allantoin (as known as Moogoo Udder Cream®) versus aqueous cream in reducing RISR, improving pain, itching and quality of life in this patient group. One group will receive Moogoo Udder Cream®. Another group will receive aqueous cream. Outcome measures will be collected using patient self-administered questionnaire, interviewer administered questionnaire and clinician assessment at commencement of radiotherapy, weekly during radiotherapy, and four weeks after the completion of radiotherapy.

**Discussion:**

Despite advances of radiologic advances and supportive care, RISR are still not well managed. There is a lack of efficacious interventions in managing RISR. While anecdotal evidence suggests that Moogoo Udder Cream® may be effective in managing RISR, research is needed to substantiate this claim. This paper presents the design of a double blind randomised controlled trial that will evaluate the effects of Moogoo Udder Cream® versus aqueous cream for managing in RISR in patients with cancer.

**Trial registration:**

ACTRN 12612000568819

## Background

Radiotherapy remains an essential treatment for patients with cancer and is associated with a number of short term and long term side effects [1]. One of these side effects includes radiation-induced skin reactions (RISR), also known as radiation dermatitis, which affects up to 90 % of cancer patients receiving radiotherapy [2-4]. Approximately, 85 % of these patients experience a moderate-to-severe skin reaction [5,6]. The reactions are the combined result of a decrease in functional stem cells, changes in the skin’s endothelial cells, inflammation, and skin cell necrosis and death of the skin [7]. Radiation-induced skin reactions are often characterised by oedema, erythema, changes in pigmentation, fibrosis and ulceration [8]. Signs and symptoms may include skin dryness, itching discomfort, pain, warmth, and burning [9]. Radiation-induced skin reactions have an impact on pain and quality of life in this patient group [10], and if severe, may necessitate changes to the patient’s radiation schedule [11]. Therefore, managing skin reactions is an important priority in caring for this patient group [9].

The development of RISR may begin immediately, with increasing toxicity occurring at 2–3 weeks, with effects accumulating across the course of treatment, and may persist up to 4 weeks after treatment ends [4]. Hypothesised risk factors influencing RISR reported in the literature are both intrinsic or extrinsic [12]. The intrinsic factors are age, general health, ethnic origin, co-existing diseases, UV exposure, hormonal status [12] and genetic factors [13]. The extrinsic factors include the dose, volume, and number of fractions of radiation, radio-sensitizers, concurrent chemotherapy and the site of treatment [12]. Of these hypothesised factors, smoking status [14] and BMI [14,15] are the major influencing factors supported by empirical data. A range of interventions are used for prophylaxis and management of these reactions. These interventions include (i) topical preparations (both steroidal and non-steroidal), (ii) dressings, (iii) systematic treatment such as amifostine, oral hydrolytic enzymes, pentoxifylline and zinc supplement, (iv) alternating modes of radiation delivery. The latest published systematic review including 39 trials before 2008 reported that only topical corticosteroid agents, among other interventions mentioned above, were found to significantly reduce the severity of some RISR, but not the levels of pain and itching [5]. Further, it is not yet clear which corticosteroid is superior to other non-steroidal agents [5]. This systematic review, together with a number of other previous reviews concluded that the uses of these interventions are not yet supported by conclusive evidence and warrant further investigations [4,5,10,16,17]. Current evidence indicates that there is a paucity of conclusive evidence which can inform health professionals on effective skin management of RISR [18,19].

A natural oil-based emulsion, as known as Moogoo Udder Cream®, is a Queensland owned product that comprises allantoin, purified water, sweet almond oil, olive oil, rice bran oil, emulsifying wax, milk protein, aloe vera, vitamin E, glycerol caprylate, piroctone alamine and guarsilk. Anecdotal reports by patients with RISR and radiation oncologists in a number of Australian cancer centres suggest that Moogoo Udder Cream® may be effective in promoting healing, comfort, and pain relief. This product is being increasingly used in some other Australian cancer centres in for managing RISR, however there is not yet empirical evidence supporting this claim. This study aims to investigate the effects of Moogoo Udder Cream® against aqueous cream (which is current standard of care) in patients with RISR.

## Objective of the study

The aim of this study is to assess the efficacy of Moogoo Udder Cream® against aqueous cream for managing RISR in patients with breast cancer/lung cancer and head and neck cancer receiving radical radiotherapy.

## Methods and materials

### Design

A double-blind randomised controlled trial design will be used in this study.

### Research questions

1. Is there any difference in incidence of Grade 2,3 and 4 RISR between patients with breast, lung and head and neck cancers who receive Moogoo Udder Cream® and those who receive aqueous cream at week 5?

2. Do patients with breast, lung and head and neck cancers who receive Moogoo Udder Cream® for their RISR have a different level of quality of life compared to those who receive aqueous cream at week 5?

3. Do patients with breast, lung and head and neck cancers who receive Moogoo Udder Cream® for their RISR have a different level of pain compared to those who receive aqueous cream at week 5?

4. Do patients with breast, lung and head and neck cancers who receive Moogoo Udder Cream® for their RISR have a different level of itching compared to those who receive aqueous cream at week 5?

5. Is there any difference in time to grade 2, 3 and 4 of RISR between patients with breast, lung and head and neck cancers who receive Moogoo Udder Cream® and those who receive aqueous cream?

6. Are there any differences in RISR, pain, itch and quality of life between groups at all other time points assessed (i.e. week 1,2,3,4,6 of radiation treatment, and 4 weeks post treatment completion)?

### Sampling frame

Participants in this study will all be patients receiving radical radiotherapy for lung cancer, breast cancer and head and neck cancer at the Royal Brisbane and Women’s Hospital (see Table 1). A sample of consecutive eligible and consented patients will be recruited into the study. The research nurse will screen all patients for eligibility at the Radiation Treatment Department over the study duration period.

**Table 1 T1:** Recruitment criteria for this study

**Recruitment criteria**	
**Inclusion criteria**	**Exclusion criteria**
· Age >18 years	· Patients who are unable to consent
· Patients who have a definitive diagnosis of breast cancer, lung cancer or head and neck cancer	· Patients with pre-existing skin rash, ulceration or open wound in the treatment area
· Patients who are receiving radiotherapy (>50 Gy) either as primary treatment or postoperative treatment to their chest, breast or head and neck.	· Patients with known allergic and other systemic skin diseases even not directly affecting irradiated fields.
	· Patients with any known allergic reactions towards any ingredient of either the Moogoo Udder Cream® or the aqueous cream and failed the patch test.

### Baseline characteristics

Baseline characteristics are demographic and clinical variables which include personal factors and radiotherapy factors (see Table 2). These variables are expected to be important for explaining the primary and secondary outcomes in this patient group.

**Table 2 T2:** Summary of baseline characteristics and data collection

**Independent variables**	**Data collection**
Personal factors	Age
	Gender
	Ethnicity
	Stage of cancer (Staging, nodal involvement)
	Comorbidity
	Prior chemotherapy/radiotherapy
	Concurrent chemotherapy/biotherapy (e.g. monoclonal anti-bodies)
	Body mass index
	Smoking
	Cup-size (breast and axilla)
Radiotherapy factors	Daily dose (Gy/fraction)
	Planning target volume (cm3)
	Total dose to region of interest
	Site of radiotherapy
	Radiation technique (External beam via Tomotherapy/Linear accelerator)
	Boost (Yes or no)
	Number of boost treatments

### Outcomes

#### Primary outcome

##### Severity of skin reaction (assessment by the clinician)

The Common Terminology Criteria for Adverse Events (CTCAE- Version 4.0) will be used to assess the severity of RISR [20]. This instrument is well used and well validated in radiation oncology for assessing radiation dermatitis [21]. This assessment will be undertaken weekly by a research nurse with extensive clinical experience in radiation oncology on a weekly basis during their weekly progress evaluation clinic during their treatment period. This scoring system is widely used in practice and research. The research nurse will be instructed prior to the beginning of the study to score the worst toxicity present, at the time of assessment within the treatment field.

### Secondary outcomes

#### Quality of life (skin specific) (self-administered by the patient)

Skindex-16 is a 16-item self-administered survey instrument developed by Chren and her research team in 2001 to measure the effects of skin condition on quality of life [22,23]. Skindex-16 comprises three scales to assess patient emotion, symptoms and functioning. Item responses are standardized from 0 (no effect) to 100 (maximal effect). The scale demonstrated good psychometric properties: reliability at 72 hours (r = 0.68-0.90) and internal consistency (Cronbach’s Alpha = 0.76-0.86). This tool has been increasing used in patients with skin toxicities resulted from their anti-cancer treatment [23-25]. Permission to use this tool has been granted by the author.

#### Modified brief pain inventory (self- administered by the patient)

This study will use three measures from the Brief Pain Inventory (BPI), those of the average, best, and worst pain, and pain relief scores from the preceding seven days [26]. The participant will be asked to rate their pain level at the irradiated area. The time of interest of the original BPI is modified from “the past 24 hours” to “the past 7 days” for the specific purpose of this study. The BPI has been selected as it is a brief and easy tool for the assessment of pain within both the clinical and research settings. It has been well validated in both the chronic pain and cancer settings. The scale of 0 to 10 is simple for patients to use and reflects common clinical assessment of pain.

#### Itching (self- administered by the patient)

Itching will be scored on a numeric analogue scale of 0–10 in the treated skin (0 = no itching at all), (10 = itching as bad as you can imagine).

#### Treatment interruptions

Treatment interruptions due to severe skin reactions will be documented throughout the study (Yes/No). This decision is determined and routinely documented by the treating medical officers.

#### Adverse events

Adverse events will be assessed by the research nurse. Adverse events will include allergic reactions from the allocated treatment and will be assessed using the Common Toxicity Criteria for Adverse Events version 4.0. (CTCAE v4) [18].

### Sample size

A sample size of at least 81 in each arm would be required to detect a 20 % difference in the skin reactions scores using a 2-sided significant level of 0.05 and a power of 80 %. Assuming that approximately 5 % will be lost to follow-up; an additional 5 in each group will be required so the final sample will require 172 patients (86 per arm). All eligible patients will be approached consecutively. According to the local statistics of RBWH Cancer Care Services [27], 746 patients receive radical radiotherapy for breast cancer, lung cancer and head and neck cancer over a twelve-month period. Thus, the sample size proposed is achievable over a period of seven months.

### Randomisation

Eligible and consenting patients will be randomly allocated to the intervention group to receive Moogoo Udder Cream®, or the control group to receive aqueous cream.

### Sequence generation

Blocked randomisation will be performed, with a block size of six, by a computer generated random number list prepared by an investigator who has no clinical involvement in the trial. Stratification by irradiated sites (breast, lung or head and neck), BMI categories (underweight <18.50, normal = 18.50-24.99, overweight =25-29.9, obesity > 30) and smoking status (smoking and non-smoking) will be carried out.

### Allocation concealment and blinding

After the research nurse has obtained the patient’s consent. The research nurse will then allocate participants to either receive Cream 1 (Group 1), or receive Cream 2 (Group 2) according to the generated sequence. This proposed study is a double-blind study. Blinding will be accomplished by not disclosing to the research nurse, medical officers, radiation therapists, nurses or participants which preparation used for skin treatment for each of the participants.

Both topical preparations (Moogoo Udder Cream® and aqueous cream) are white in colour, have similar consistency, and have no distinct odour. There are no other differentiating features. Both topical preparations will be provided and coded as Cream 1 or Cream 2 by the manufacturer in identical containers. The manufacturer will only disclose what Cream 1 and Cream 2 are at the completion of data collection. Subsequently, baseline data will be collected.

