### Data collection

Table 3 outlines the measures used in this study. At baseline and weekly during treatment, data will be collected when patients are in the radiation oncology department. At completion of radiotherapy, patients will be given the diaries to complete at home at week 1, week 2 and week 3 post-treatment. The research nurse will contact the patient via telephone to remind them to complete the diaries. At week 4 post-treatment, all patients who have completed their treatments will return to the radiation oncology department for a routine medical review. At this time, they will be asked to complete the final questionnaire and have the severity of their skin reaction assessed by the research nurse.

**Table 3 T3:** Table of study measure

**Measures**	**Administered by**	**Baseline (i.e. Day −7 to Day 0 of radiation treatment)**	**Weekly during treatment (i.e. Day 5, 10, 15, 20, 25, 30 of radiation treatment)**	**Week 1, week 2 and week 3 post treatment (i.e. Day 5, 10, 15 post radiation treatment)**	**4 weeks after radiation treatment Review appointment (Face to face)**
Personal factors (see Table 1)	Research nurse	*			
Radiotherapy factors (see Table 1)	Research nurse	*			
CTCAE	Research nurse	*	*		*
Modified Brief Pain Inventory	Patient	*	*	*	*
Itching	Patient	*	*	*	*
Skindex-16	Patient	*	*	*	*

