### Data analysis

Patient characteristics between arms will be compared using the chi-square test for discrete variables and the *t*-test for continuous variables. Acute reactions will be evaluated using Kaplan-Meier actuarial plots (time to event) with the log-rank test for significance. Grade reaction plots at the particular time points (weeks) will be plotted and compared with 95 % confidence intervals for both arms. Uni-variate regression models will determine the significance of factors to be included in the multivariate regression model. A generalized linear interactive modelling package (GLIM4) will be used.

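### The cream code may be opened once data collection ends, so the plan permits cleaning and choice of the adjusted model with the test arm known

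*Protocol article*

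**What the plan says.** Four statements in the protocol article bear on this point.

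- **Release of the code** (Allocation concealment and blinding): "The manufacturer will only disclose what Cream 1 and Cream 2 are at the completion of data collection".
- **Form of the code** (same section): "Both topical preparations will be provided and coded as Cream 1 or Cream 2 by the manufacturer in identical containers". There are two labels for the whole trial.
- **Who is blinded** (same section): "Blinding will be accomplished by not disclosing to the research nurse, medical officers, radiation therapists, nurses or participants". Data managers and analysts are not named.
- **Choice of the adjusted model** (Data analysis): "Uni-variate regression models will determine the significance of factors to be included in the multivariate regression model".

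The last scheduled data come from the review four weeks after radiotherapy. The Data collection section says of that visit: "At this time, they will be asked to complete the final questionnaire and have the severity of their skin reaction assessed by the research nurse". The article mentions neither a database lock nor data cleaning, and it does not say when the model is to be fixed.

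**The concern.** The article does more than leave the timing of unblinding to another document. It names a trigger, and that trigger is the end of data collection. Some work that can affect the result normally comes after that point: resolving queries, settling doubtful records, and here also selecting covariates from the observed data.

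If the identity of the creams is known during that work, the people doing it know which choices move the estimate towards the test product. The influence can be unintended. Blinding protects the assessments while patients are followed, and the same protection is available for the analysis at almost no cost, because two arms can be compared fully under neutral labels.

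**Working it through.** No figure in the plan is in dispute, so the check sets the sections side by side and follows the order of events.

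1. **Earliest permitted disclosure.** The trigger is completion of data collection. Under the Data collection section and Table 3, the last item is the questionnaire and skin assessment at the review four weeks after radiotherapy. Read literally, the code may be opened once the last patient has had that visit.

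2. **What one disclosure reveals.** The code has two labels, so naming Cream 1 identifies Cream 2 and unblinds every patient: 2 × 86 = 172 under the Sample size section. The article is aware of this property. Its Discontinuation section warns that unblinding one patient could give away the products for later patients.

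3. **Who is still protected afterwards.** While the manufacturer holds the key, an analyst is blind in practice, named or not. After disclosure that protection ends. The list of blinded roles does not include an analyst or data manager, and the article does not say to whom the manufacturer discloses. Nothing shown keeps the analysis blinded from then on.

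4. **What is still to be decided.** The covariate rule depends on univariate results, so it cannot be completed before outcome data exist. Table 2 lists 10 personal factors and 7 radiotherapy factors: 10 + 7 = 17 candidates. The article states no significance threshold; one may stand in an analysis plan that is not shown.

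5. **Comparison of the two points in time.** Disclosure is permitted from the end of collection. Final model selection needs the collected data, so it ordinarily falls at or after that same moment. Nothing in the article requires selection to come first. The stated rule therefore allows the adjusted model to be chosen with the test arm known. The same holds for cleaning, if cleaning is not counted as part of collection.

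6. **What knowledge of the key adds.** Univariate screening relates factors to outcome and does not need to know which cream is which. The grouping into Cream 1 and Cream 2 is in the data anyway, so anyone with the allocation list can see how the difference between groups changes from one covariate set to another. The key adds one thing: which direction favours the test product.

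The size of the resulting bias depends on how the choices are made in practice, and the document gives nothing from which to compute it. The count of 17 describes the room for choice, not the harm from early disclosure.

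**The case against.** The strongest case on the other side has four parts.

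- **The sentence is a safeguard.** It bars disclosure before data collection is complete and so protects outcome assessment. That is true, and the wording is not contradicted elsewhere. It protects assessment but does not extend to analysis.

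- **Lock, cleaning and order of analysis belong in the full protocol or analysis plan.** This stands. Their absence from an article is not an error, and this point does not rest on it. It rests on the trigger that the article does state.

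- **The sequence is not given.** A reader might infer that the code will be opened before lock and that cleaning and covariate selection will be done unblinded. The document does not support that. It gives no lock date and no cleaning procedure, and completion of data collection could be meant to include entry, cleaning and lock.

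- **The real weakness is data-driven selection.** This stands in part. Masked labels hide only the favourable direction. Selecting covariates by univariate significance remains a weakness under any disclosure date.

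A reader might also infer that the primary skin outcome is wholly open at disclosure. That goes too far. The research questions list incidence of higher-grade reactions at week 5, time to those grades, and the other time points as separate questions, and clinician-graded CTCAE severity is named as the primary outcome.

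**Conclusion.** The point holds as a weakness in the stated disclosure rule. The plan permits cleaning and choice of the adjusted model after the test arm is known, because release of the code is tied to the end of data collection, one disclosure unblinds everyone, no analyst is listed as blinded, and covariates are picked from the collected data. It is not evidence that the analysis would be done unblinded.

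The conclusion rests on reading completion of data collection in its ordinary sense, and on no other document setting a later trigger. If the full protocol or analysis plan already ties disclosure to lock and a fixed model, only the article's wording needs to be aligned. The size of any bias cannot be computed. The change is worth making because it is cheap and closes an avoidable route to bias.

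**What to change.** Replace the disclosure sentence in Allocation concealment and blinding with a rule of this kind:

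*The manufacturer will reveal the identity of Cream 1 and Cream 2 only after (a) the database is locked, (b) the analysis model and its covariates are fixed in writing, and (c) the primary and secondary analyses have been run as Cream 1 versus Cream 2.*

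The manufacturer already holds the key, so no new procedure is needed. The cost is one sentence and a short delay in disclosure, equal to the time needed for lock and the first run of the analyses.

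The new trigger removes knowledge of the favourable direction from cleaning and model choice. It does not cure selection of covariates by univariate significance, even with the chosen set recorded before disclosure. That needs covariates named before outcome data are examined.
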